#### Data analysis

Times to diagnosis, treatment and other continuous outcomes will be compared using simple *t* tests. Categorical outcomes, such as proportions of emergency admissions, will be compared using Poisson regression. Survival will be compared using proportional hazards regression. Patient satisfaction will be recorded in categorical outcomes, and will be compared using non-parametric tests.

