### Randomisation

Intervention is at an institutional level; individual patients will not be randomised. Half-day sessions will be randomised to intervention or standard practice, using a randomisation list provided by the study statistician. This is in line with previous studies that have examined the timing or order of X-ray reading but where all examinations are requested as part of routine clinical care and receive reports from the same practitioners [30].

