### Outcome measures

The primary outcome is to test the impact of radiographer immediate reporting of GP CXRs, with immediate CT where appropriate, on time from performance of the CXR to treatment (with intermediate time points)/discharge for lung cancer.

Secondary outcome measures include:Measurement of the effect on the speed of the lung cancer pathway:
(i)6-and 12-month survival (lung cancer and all-cause)(ii)Number of emergency admissions for lung cancer(iii)Performance status at time of decision to treat(iv)Stage at diagnosis of lung cancer
Measurement of the effect of the pathway on efficiency including:
(i)The impact of immediate GP CXR reporting on the number of urgent respiratory cancer (2WW) referrals(ii)The accuracy and usefulness of radiographer CXR reporting in clinical practice(iii)The cost-effectiveness of radiographer reporting(iv)The influence of immediate GP CXR reporting, with immediate CT where appropriate, on the number of first 2WW appointments with all radiology results available
Measurement of the number of repeat CXRs performed in a timely fashion for suspected infectionThe effect of immediate reporting of GP CXRs on patient satisfaction

In addition to comparison as per randomisation within Homerton University Hospital, primary outcomes will be compared with a neighbouring hospital, Newham University Hospital.

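### Half-day sessions are randomised but the named tests are patient-level. This is negligible for cancer outcomes but can matter for outcomes counted over many films, and the Poisson variance and the ordinal outcomes need a stated method

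*Protocol article*

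**What the plan says.** The Randomisation section is explicit about the unit: "Intervention is at an institutional level; individual patients will not be randomised", and "Half-day sessions will be randomised to intervention or standard practice, using a randomisation list provided by the study statistician".

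The Data analysis section then names the methods. For continuous outcomes, "Times to diagnosis, treatment and other continuous outcomes will be compared using simple" t tests. For categorical outcomes, "Categorical outcomes, such as proportions of emergency admissions, will be compared using Poisson regression". For survival, "Survival will be compared using proportional hazards regression". Patient satisfaction goes to non-parametric tests. Neither that section nor Sample size mentions the session, a cluster-robust variance or a design effect. The variance estimator for the Poisson model is not stated.

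The Outcome measures section lists among the secondary outcomes "Performance status at time of decision to treat" and "Stage at diagnosis of lung cancer". Data analysis names neither of them. They reach Poisson regression only because they are categorical.

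**The concern.** Three matters arise from the same short section.

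- **Unit of analysis.** All patients X-rayed in one half-day share an allocation. If their outcomes are also correlated, for instance through the reader or the staffing of that half-day, a test that treats patients as independent gives intervals that are too narrow. The article gives some reason to expect this. Reporting radiographers have between 1 and 8 years of experience and arrange further imaging themselves, and in the immediate arm they book the six-week repeat film.
- **Poisson model for a yes/no outcome.** The Poisson likelihood assumes a variance equal to the mean, which is larger than the binomial variance. With model-based standard errors the intervals are too wide and power is lost.
- **Ordered outcomes.** Stage and performance status are ordered categories. Poisson regression does not model the ordering, and a robust variance would not change that.

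The first two errors run in opposite directions and affect different outcomes, so they have to be sized separately.

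**Working it through.** **1. Does the sample size allow for clustering?** Inputs from Sample size: two-sided 5%, 80% power. Per-group n = 2 × (1.96 + 0.842)² × SD² / difference², where 2 × (1.96 + 0.842)² ≈ 15.70.

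- 11 days, SD 14: 15.70 × 196 / 121 = 25.4, so 26 (stated 26).
- 12 days, SD 14: 15.70 × 196 / 144 = 21.4, so 22 (stated 22).
- 7 days, SD 15: 15.70 × 225 / 49 = 72.1, so 73 (stated 73).
- External comparison, 50 against 25 cancers: power 0.894 (stated as close to 90%).

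All four figures reproduce with individual-level formulas, so the design effect (DE) used was 1.

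**2. Clustering for cancer outcomes.** The article gives about 50 cancers a year and a 12-month study. The number of sessions is not given; 400 to 500 is an assumption. Cancers per session: 50/500 = 0.10 to 50/400 = 0.125. With so few per session, DE = 1 + (mean cancers per session) × ICC.

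- ICC 0.01 to 0.05: DE 1.001 to 1.006.
- ICC 0.1: DE 1.010 to 1.0125; n stays at 26 per group, power at 26 is 80.4% to 80.5%, and the true size of a nominal 5% test is 5.1%.
- ICC 1, the extreme: DE 1.10 to 1.125, n 28 to 29, test size 6.2% to 6.5%.

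For everyone referred to the pathway, taking the stated 2 × 73 = 146 over 500 sessions, DE is 1.003 to 1.029 for ICC 0.01 to 0.1, and n is 73 to 75 per group.

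**3. Clustering for outcomes counted over all films.** DE = 1 + (m − 1) × ICC; true size = 2 × [1 − Φ(1.96/√DE)]. Films per session (m) and ICC are both assumptions.

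| m | ICC | DE | Size of nominal 5% test |
|---|---|---|---|
| 10 | 0.01 | 1.09 | 6.0% |
| 10 | 0.05 | 1.45 | 10.4% |
| 30 | 0.01 | 1.29 | 8.4% |
| 30 | 0.05 | 2.45 | 21% |

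**4. Poisson variance on a yes/no outcome.** With n per arm and common risk p, the model-based variance of the log risk ratio is 2/(np) and the binomial variance is 2(1 − p)/(np). The ratio of standard errors is 1/√(1 − p). The risks below are assumptions.

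- p = 0.3: 1/√0.7 = 1.195; size = 2 × [1 − Φ(1.96 × 1.195)] = 1.9%.
- p = 0.5: 1/√0.5 = 1.414; size = 0.6%.
- p = 0.1: 1.054; size 3.9%.

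In simulation (200,000 replicates, 25 per arm, 60% against 30%), power was 28% with model-based and 51% with robust (binomial) variance.

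**The case against.** The strongest reply is that a condensed article may leave the variance estimator to the analysis plan. Poisson regression with robust variance is a valid route to risk ratios, and nothing here rules it out. That stands: a reader might infer that the Poisson intervals are wrong as planned, but the article does not say which variance is used, so the figures in step 4 are conditional. The event risks are also assumed, and the error would be conservative.

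A reader might also infer that ignoring sessions undermines the primary comparison or its sample size. Step 2 shows that it does not.

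Nor does the clustering point extend to every secondary outcome:

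- Report accuracy compares the radiographer's and the radiologist's reports of the same film. It is paired within film, so the between-session design effect does not describe it.
- Repeat films concern only patients with suspected infection, so fewer count per session than the 10 to 30 assumed for all films.
- The satisfaction survey is postal and anonymous, and the printed questions record no date or session.

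A shared reader within a session is plausible but not stated. Control films are read in the next reporting session, and nothing says that one person covers a session.

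Finally, stage and performance status are not named under Poisson regression. That is correct, but no other method in Data analysis fits ordered outcomes naturally.

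What remains is that the randomised unit is stated, the analyses are named at patient level, and the word simple before the t tests leaves no evident place for a session term.

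**Conclusion.** The point holds in limited form. The named analyses do not follow the randomised unit. The consequence is negligible for the primary and other cancer-only outcomes (DE at most about 1.01 for ICC up to 0.1, if there are 400 to 500 sessions). It is potentially material for 2WW referrals and less so for repeat films. The range of 6% to 21% for a nominal 5% test rests wholly on assumed session size and ICC and is not an estimate for this trial.

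The Poisson issue is conditional on model-based variance. If that were used, it would lose power for yes/no outcomes such as emergency admission, with only about 25 cancers per arm. Stage and performance status fall under the Poisson rule by class, not by name, and an ordinal model suits them better.

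This is worth correcting because it is cheap. It is no reason to doubt the planned size of the trial.

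**What to change.** State in the analysis plan that, for between-arm comparisons within the intervention hospital:

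- the half-day session in which the film was taken is the randomised unit, and standard errors are robust (sandwich) and clustered on it;
- this includes the Poisson models of yes/no outcomes, reported as risk ratios with 95% intervals, so that one choice handles both the clustering and the Poisson variance;
- stage and performance status are compared with an ordinal method, such as proportional-odds regression, with the same clustering.

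Do not apply this to report accuracy, which needs a paired analysis. Apply it to the satisfaction survey only if replies can be linked to a session; as printed, the form gives no link.

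The cost is analysis wording. The session can be derived from the date and time of each chest X-ray and the randomisation list, provided that the de-identified data set carries a session code. The sample size need not change.

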#### Patient satisfaction

Patients referred for a CXR from GP will be identified by the radiology administration team, as is current practice. Eligible patients will have a Patient Satisfaction Survey posted to their home address, with a stamped self-addressed return envelope. No patient-identifiable data will be collected. Comparison will be made between patients who received an immediate and routine CXR report. The Patient Satisfaction Survey to be used has been included as an Appendix.

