**Methods:**

A two-way comparative study that will compare the time to diagnosis of lung cancer for patients. Internal comparison will be made between those who receive an immediate radiographer report of a GP CXR compared to standard radiographer GP CXR reporting over a 12-month period. External comparison will be made with a similar, neighbouring hospital trust that does not have radiographer CXR reporting. Primary outcome is the effect on the speed of the lung cancer pathway (diagnosis of cancer or discharge). Secondary outcomes include the effect of the pathway on efficiency including the number of repeat CXRs performed in a timely fashion for suspected infection and the effect of immediate reporting of GP CXRs on patient satisfaction.

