## Appendix

### Patient Satisfaction Survey

Homerton University Hospital strives to offer effective, patient-focused healthcare. In order to improve services we would value your feedback on your experiences when you recently attended the radiology department for a chest X-ray. Please indicate your response to each question by circling the appropriate answer.

All answers are anonymous and confidential. If you have any questions please contact [name], radiographer, on [name].

Please return the completed survey in the stamped, self-addressed envelope provided.

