**Q4 When were you told that the results of your chest X-ray would be available?**

Immediately – given by a radiographer

Immediately – to contact my GP

Next day – to contact my GP

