**Q6 How do you feel about how you were told that you needed further tests?**

I did not need any further tests

It was done sensitively

It could have been done a bit more sensitively

It could have been done a lot more sensitively

**Q7 How did you feel about needing further tests**?

Frightened

Angry

Upset

Pleased that something was happening

Prefer not to say

Any comments?

**Q8 Would you have liked to be contacted by your own GP (Doctor) before the CT scan – even if this meant a delay to your scan?**

Yes

No

Not sure

Prefer not to say

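### The satisfaction survey has no closed satisfaction question that every recipient can answer, and nothing printed on the form shows the randomised session

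*Protocol article*

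**What the plan says.** The Abstract of the protocol article names among the secondary outcomes "the effect of immediate reporting of GP CXRs on patient satisfaction", and Outcome measures repeats this. Under Patient satisfaction, the radiology administration team identifies eligible patients and the survey is posted to their homes. The mailing is not limited to patients who had a CT or any other further test. The same section says "No patient-identifiable data will be collected. Comparison will be made between patients who received an immediate and routine CXR report", and it names the form in the Appendix as the survey to be used. That form tells patients "All answers are anonymous and confidential".

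Data analysis adds: "Patient satisfaction will be recorded in categorical outcomes, and will be compared using non-parametric tests".

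Off-protocol radiographer reporting says that a patient whose X-ray worries the performing radiographer gets an immediate report whichever way the session was allocated. Such patients stay in the intention-to-treat analysis, and a sensitivity analysis leaves them out.

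**The concern.** Every patient in an intervention session is meant to have the X-ray reported before leaving the department, so the effect on satisfaction is a question about all of them. That includes the patients with nothing further to investigate. The Discussion itself expects a gain from an early alternative diagnosis and less anxiety. If the form asks such patients nothing about their satisfaction, the trial cannot show that gain or its absence.

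The second issue is the grouping. Randomisation is by half-day session. An anonymous form with no session or arm printed on it can be placed in a group only by what the patient ticks. Once anonymous forms have come back, neither defect can be repaired at analysis.

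**Working it through.** The article gives no sample size, response rate or effect size for the survey, so there is no planned figure to reproduce. The check is a reading of the printed form, item by item.

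**Step 1. What each question can supply**

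- Questions 1 to 3: gender, age group and ethnic group. Demographic.
- Question 4, "When were you told that the results of your chest X-ray would be available": factual, asked of everyone.
- Question 5, whether further tests were needed: factual, asked of everyone.
- Question 6, how sensitively the need for further tests was conveyed: a rating, but only for patients who needed them; the others have an opt-out answer.
- Question 7, "How did you feel about needing further tests": a feeling, again only for patients who needed further tests.
- Question 8, whether GP contact before the CT would have been preferred: a preference that presupposes a CT.
- Question 9, the wait for CT results: factual, CT patients only.
- Question 10, flexibility of booking: a rating, conditional on having had an appointment; its first answer option refers to a scan.
- Question 11: free text, open to everyone, not categorical.

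Count: 3 demographic + 3 factual (4, 5, 9) + 4 conditional evaluative or preference items (6, 7, 8, 10) + 1 free text = 11. Closed satisfaction ratings that apply to every recipient: 0. No closed item asks how satisfied the patient was with how or when the X-ray result was given, which is what the intervention changes.

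**Step 2. How many recipients this leaves out**

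Let p be the share of recipients who have further tests. The share with no closed item on their experience of the report is 1 − p. Question 10 is set aside here because it concerns booking only. The article gives neither p nor the number of GP X-rays, so p is assumed:

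- p = 5%: 1 − 0.05 = 95%
- p = 10%: 90%
- p = 20%: 80%
- p = 30%: 70%

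The share exceeds one half whenever p is below 50%.

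**Step 3. Why the remaining items do not give a randomised comparison**

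Questions 6 to 8 are answered by a group defined after randomisation. Under Intervention and Control, a patient with a suspicious X-ray is offered a CT at once in one arm and a CT appointment through the secretaries in the other. Under Repeat chest X-ray for suspected infection, the reporting radiographer arranges the repeat in the immediate arm and the GP requests it in the standard arm. The way patients learn of further tests, and possibly who reports having had them, thus depends on the arm. Perfect arm labels would not remove this.

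**Step 4. What the form shows about allocation**

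The form has no session, date or arm field. The only closed item that bears on group for every recipient is question 4. Its limits are:

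- It asks what the patient was told, not what was done.
- It has no answer for a patient who cannot remember, although questions 9 and 10 do.
- Its only later option is the next day, whereas Control allows up to one working day, so a patient X-rayed just before a weekend may have no fitting answer.
- A flagged patient in a control session would correctly tick an immediate answer and so fall into the immediate group.

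From question 4 alone, neither the intention-to-treat comparison nor the sensitivity analysis described under Off-protocol radiographer reporting could be carried out for satisfaction.

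**The case against.** The strongest reply concerns allocation. The radiology administration team posts the forms and can know each patient's session. A promise of anonymity does not exclude an arm mark, such as two print versions or a marked return envelope. A condensed article may well leave mailing detail to the full protocol, and nothing says that question 4 will define the groups. This stands. A reader might infer that comparison by arm is impossible; the documents do not support that, because a mark is neither described nor excluded and question 4 gives at least a rough indicator.

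A reader might also infer that the plan fixes an as-treated comparison. That goes too far. The Abstract and Trial design describe the session-randomised comparison in much the same language of patients receiving a report, so the verb may be shorthand for arm. What remains is an ambiguity over the flagged control-session patients.

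Two further inferences fail. Non-parametric need not mean rank tests, since tests for unordered categories are often counted under that name, so the answers to question 7 do not contradict Data analysis. And the absence of a not-applicable answer to questions 7 and 9 does little harm, because questions 5 and 6 already identify patients without further tests.

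Lastly, further tests include repeat X-rays and extra views as well as CT, so the affected share cannot be taken as known. This also stands. None of these replies touches the count in step 1, because the form itself is printed in full and named as the instrument.

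**Conclusion.** The point holds in two parts of unequal strength.

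- **Firm:** none of the 11 questions is a closed satisfaction item for every recipient. The secondary outcome cannot be estimated for all patients X-rayed on GP referral, and the conditional items describe a post-randomisation subset whose pathway differs by arm. This rests on the printed form alone.
- **Conditional:** unless forms carry a mark that the article does not describe, group membership rests on self-reported question 4, which does not recover the randomised session. The wording under Patient satisfaction leaves open whether flagged control-session patients are analysed as allocated.

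That most recipients are left without a relevant closed item is an assumption, true if fewer than half have further tests. No size can be put on misclassification through question 4, because the documents give no error rate. The consequence is confined to one secondary outcome of a study that calls itself a pilot; the primary outcome is unaffected. The change is still worth making because it is cheap and cannot be made once forms are returned.

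**What to change.** 1. Add one ordinal question for every recipient on satisfaction with how and when the X-ray result was given, for example on five points, and name it as the satisfaction outcome.
2. Put a non-identifying session-allocation mark on each posted form. If the full protocol already provides for this, say so.
3. State that satisfaction is compared by randomised session, in line with Off-protocol radiographer reporting. To allow the planned sensitivity analysis here too, let the mark also distinguish flagged patients, if that can be done without identifying anyone.
4. Report questions 6 to 10 descriptively among the patients to whom they apply.

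The cost is a slightly longer form, a reprint and possibly a minor approval notification. Forms returned before the change cannot be repaired; their lack of a general rating and of a session mark should be reported as a limitation.

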#### Health economic assessment

Adaptation of a health economic model that examined the impact of radiographer CXR reporting on the lung cancer pathway will be performed [35]. The model for this project will map out the care pathways following standard reporting and immediate reporting. It is assumed that differences in time to treatment will affect severity and, hence, costs and quality of life. Costs will be calculated from an NHS perspective, covering a 1-year period, and include X-ray reporting time, CXR cancer and non-cancer diagnostic accuracy, subsequent care costs, as well as reading and supervision costs. The cost per case detected will be reported. Quality-of-life scores will be obtained from the academic literature for different cancer stages and these will be used to generate quality-adjusted life years (QALYs). One-way and probabilistic sensitivity analyses will be conducted to assess the impact on costs and cost-effectiveness of changing parameters in the model. Due to the timing of the intervention in relation to the lung cancer pathway there may be no meaningful difference in QALYs for the internal comparison. The reduction in time to a non-lung cancer diagnosis may be a worthwhile improvement in quality of life.

## Discussion

The current study will determine the effect of immediate reporting of CXRs referred from GP, with immediate CT where appropriate, on the time to diagnosis of lung cancer. Although only one part of the patient pathway, immediate GP CXR reporting could positively impact lung cancer diagnosis and outcomes in at least three ways: firstly, by providing an immediate CXR report and initiating earlier further investigation including CT, the time to diagnosis will be shortened. There is debate within the academic literature as to the significance of this in terms of improvements in early survival times, performance status and reducing emergency admissions [34]. The current study will examine this, both with internal and external comparison. Secondly, the efficiency of the service may be improved by reducing the number of lung cancer pathway referrals through early provision of an alternative diagnosis, which in turn means less time for patient anxiety and distress. Thirdly, the proposal may release consultant radiologist time that can instead be used to interpret more complex cross-sectional imaging and support interventional procedures including lung biopsy. A reduction in average time to diagnosis for lung cancer will help centres meet the ambitious target of 90% of lung cancer patients definitively diagnosed within 28 days by 2020 [14].

Diagnostic capacity is a significant barrier to improved outcomes for cancer patients [14, 36], with prompt radiology reports a particular issue across England [15, 18].

The limitations of the current study include the fact that the intervention occurs only at a single clinical site at which the diagnostic aspect of the lung cancer pathway is already relatively streamlined. This is addressed by external comparison with a neighbouring hospital with similar patient characteristics and a comparable number of lung cancers diagnosed annually.

